## Abstract

**Introduction::**

Although the current western treatment plans for unstable angina (UA) has been optimized in past decades, UA still is a common phenotype of acute coronary syndrome and significantly influence the quality of life and endanger lives. In China, the clinical application of Chinese herb medicine is considered as an effective approach to treating UA and widely recognized by patients. In clinical practices, we found Luofengning granule (LFN-G) could improve clinical manifestations of patients with UA, but there is lack of rigorous proof of evidence-based medicine. This trial aims to further evaluate the efficacy of LFN-G in the treatment of UA.

**Methods::**

A prospective, open-label, randomized, placebo-controlled clinical will be performed. A total of 60 patients diagnosed with UA will be randomly allocated to either the treatment group or the control group with a 1:1 ratio. The participants in the treatment group will receive LFN-G treatment and the participants in the control group will receive placebo. Meanwhile, both groups continue to undergo standard western medicine treatments. The duration of interventions is 4 weeks. The primary endpoint is the incidence of major cardiac adverse events, defined as a composite of recurrent angina, acute myocardial infarction (AMI), severe arrhythmia, heart failure, and cardiac death. Secondary outcomes include Seattle angina scale score, Chinese medicine syndromes and electrocardiograph (at weeks 0, 1, 2, 4), myocardial nuclides perfusion, measurement of wall motion score index and left ventricular ejection fraction, serum inflammation factors such as C-reactive protein, high sensitive-C-reactive protein, interleukin-6, matrix metalloproteinase-9, and so on (at weeks 0, 4). In addition, some biochemical indexes of blood and hematological indexes will be used to assess the safety of treatments. Any adverse effects of the treatment will be recorded.

**Discussion::**

The results of this trial will provide compelling evidence of the efficacy and safety of LFN-G for treatment of UA and preliminarily reveal the potential mechanism of how LFN-G acts. Finally, it will widen treatment options for patients with UA.

## Introduction

1

Unstable angina (UA) is a phenotype of acute coronary syndrome (ACS), defined as myocardial ischemia at rest or minimal exertion in the absence of cardiomyocyte necrosis. Recent study indicated that the overall prevalence for angina is 3.4% in US adults ≥20 years of age.^[1]^ Approximately 10% of patients with acute chest pain present to the emergency department will be diagnosed with UA.^[2]^ Compared with the other 2 phenotypes of ACS, ST-elevation myocardial infarction (STEMI) and non-ST-elevation myocardial infarction (NSTEMI), UA exhibits a lower risk of in-hospital death.^[2,3]^ However, The Global Registry of Acute Coronary Events (GRACE) study showed there was no significant difference of 5-year total mortality among patients with 3 types of ACS (STEMI vs NSTEMI vs UA was 19% vs 22% vs 18%).^[4]^

Based on the pathogenesis of 3 types of ACS, the treatment of ACS exists differences. With vascular total occlusion caused by plaque rupture, coronary revascularization is the core of treatment of STEMI. In recent year, UA and NSTEMI were considered to present a similar clinical and electrocardiograph (ECG) features (ST-segment depressions and T-wave inversion). Clinical guidelines recommended rename the both referred to as the NSTE-ACS together and distinguishment based on high-sensitivity cardiac troponin measurements.^[2,5,6]^ In absence of coronary artery total occlusion, the treatment plans of NSTE-ACS based on the comprehensive evaluation based on clinical and ECG manifestations and myocardial biomarkers, including anti-myocardial ischemia therapy, antiplatelet or anticoagulation therapy, statin therapy, and revascularization therapy, and so on.

Although current treatment options of UA have been demonstrated for definite improvement of long-term prognosis, there still are some deficiencies. GRACE study showed post-ACS 5-year deaths most occurred after initial hospital discharge, post-discharge deaths occupied up to 97% of 5-year total deaths in UA and this figure was much higher than in STEMI (68%) and NSTEMI (86%).^[4]^ The cardiovascular prevention treatments after acute coronary syndrome (CPACS) study found only 31% of UA patients received revascularization therapy in China, which was lower than STEMI patients.^[7]^ Besides, some patients with UA manifest refractory angina, current treatments have shown some promise in angina reduction but not yet achieved the goal such as objective data like myocardial blood flow, survival, and re-hospitalization.^[8]^ These results may reflect insufficient attention were pay to the treatment of UA and current treatments for UA needs further optimization. Thus, complementary treatments for UA are urgently needed to further improve the prognosis and quality of life of patients with UA.

In addition to western medicine treatment, many Chinese patients with UA would like to seek help of Chinese herb medicine (CHM). CHM has been demonstrated to have a good clinical effect. Some meta-analysis has demonstrated the efficacy and safety of CHM.^[9,10,11]^ Luofengning granule (LFN-G) is a Chinese herbal formula based on the the theory of “endogenous wind due to collateral deficiency,” includes 6 herbs: Lumbricus (Di long), Radix Clematidis (Wei lingxian), Radix Cynanchi Paniculati (Xu changqing), Panax notoginseng (San qi), Astragalus (Huang qi), and Borneol (Bing pian). Previous observational study demonstrated that LFN-G has definite effectiveness in the treatment of UA^[12]^ associated with its’ multiple pharmacologic effects include anti-inflammatory,^[13]^ immune regulation,^[14]^ improving endothelial function,^[15]^ and coagulation regulation.^[16]^ However, there is no rigorous randomized controlled trial (RCT) that verify above conclusions. Thus, we design this prospective, open-label, randomized, placebo-controlled clinical to further evaluate the efficacy and safety of LFN-G for treating UA. This trial will provide a more compelling evidence of LFN-G and expand therapeutic options for UA.

## Materials and methods

2

### Ethical aspects

2.1

The study is conducted in accordance with the Declaration of Helsinki (Edinburgh 2000 version). The final protocol (version: November 31, 2019) of this trial has been approved by the Research Ethical Committee of Dongzhimen Hospital affiliated to Beijing University of Chinese Medicine (the ethical application has been approved). In addition, this trial has been registered in the Chinese Clinical Trial Registry (No. ChiCTR2000030533, registered March 4, 2020). Before the enrollment, all participants should sign written informed consents. If there will be any significant modification of the protocol, it should be reviewed by the research ethical committee and updated on the registry web (http://www.chictr.org.cn) timely.

### Study design

2.2

This present study is a prospective, open-label, randomized, placebo-controlled clinical trial. A total of 60 patients diagnosed with UA are eligible for enrolment and they will be randomly allocated to the treatment group or the control group in a 1:1 ratio. The study flowchart is showed in Figure 1.

**Figure 1 F1:**
[figure not shown]
Flow chart of the study design. ECG = electrocardiograph, LVEF% = left ventricular ejection fraction, MACEs = major adverse cardiac events, WMSI = wall motion score index.

### Recruitment

2.3

Two trained investigators will perform this procedure. A total 60 patients will be recruited from cardiac out-patient and ward of the Dongzhimen hospital affiliated to Beijing University of Chinese Medicine, from June 2020 until December 2022. Before the enrollment, all patients will receive a comprehensive view of informed consent, including objective, therapeutic interventions, scheduling, trial benefits, and possible risks of this trial. Only after signing a written informed consent, patients could be enrolled in this trial.

### Randomization and masking

2.4

A designated investigator of our team will use an interactive Web response system to randomly allocate participants to receive either LFN-G or placebo after enrollment in a 1:1 ratio. Randomization will be stratified by age, sex, morbid status, and comorbidities. Due to this trial is an open-label trial, so neither participants nor investigators is not masked to the treatment option.

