### Eligibility criteria

2.6

Inclusion criteria:

Diagnosed with UA by a cardiac physician.18 to 80 years old.No gender restriction.Voluntary to participate and providing written informed consents, as required by Good Clinical Practice (GCP).

Exclusion criteria:

Angina pectoris caused by noncoronary stenosis such as abnormal thyroid function, cardiomyopathy, high adrenergic state, mental stress, left ventricular load increased (hypertension, aortic stenosis), tachycardia, violent activities, and so on.Patients with stroke or undergone PCI or coronary artery bypass grafting within 1 month before enrollment.Poorly controlled hypertension (systolic pressure ≥160 mm Hg or diastolic blood pressure ≥100 mm Hg).Patients with coexistent severe heart failure (New York heart association (NYHA), Class IV) and severe arrhythmia (atrial fibrillation, atrial flutter, paroxysmal ventricular tachycardia, sinus bradycardia [heart rate <55], complete left bundle branch block).Combined liver dysfunction (defined as Alanine transaminase (ALT) and/or Aspartate aminotransferase (AST) 3 times higher than the upper limit of normal) and kidney dysfunction (defined as creatinine clearance rate less than 30 mL/min/1.73 m^2^).The terminal phase cachexia of malignant tumors.High bleeding risk, such as hemorrhagic constitution, history of hemorrhage of vital organs (brain or upper gastrointestinal tract) within 6 months, low platelet counts, abnormal coagulation function, recent active hemorrhage, and so on.Underwent surgery within 1 month.Women who are under breastfeeding, pregnancy or preparing for pregnancy.Poor compliance.Known or suspected to be allergic to experimental drugs or allergic constitution.Patients who participate in any other clinical study or take any of its investigational drugs within the last 3 months.

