### Statistical analysis

3.7

The data will be analyzed using the Statistical Package for the Social Sciences version 22.0 (SPSS 22.0, Chicago, IL). The qualitative data is analyzed by descriptive statistics, expressed by frequency and percentage; the measurement data is expressed as mean ± standard deviation and tested by *t* test or *q* test. Chi-square test is used for counting data. Spearman correlation analysis is used for single factors and logistic regression analysis is used for multiple factors. The composition ratio data is tested by *x*^2^ test. Unidirectional ordered data were tested by rank sum test. All statistical tests will be bilateral tests and *P*-values < .05 is considered to indicate statistical significance.

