## Discussion

4

UA is a common manifestation of coronary artery disease that seriously affects the quality of life and causes deaths and potential years of life lost. Current treatments for UA are still not satisfy all clinical conditions. There is a wide acceptance of CHM for treating coronary artery disease in China and it has obvious curative effect indeed. In a long-term clinical work of our team, we have found the efficacy and safety of LFN-G in treatment of UA. But we need a compelling RCT evidence to further demonstrate the benefits and risks of adding LFN-G to the standard western medicine treatment for patients with UA.

In order to evaluate the efficacy and safety of LFN-G, we design this prospective, open-label, randomized, placebo-controlled trial. In this trial, we focus on the incidence of major cardiac adverse events, angina score, quality of life, and utilize some objective physical and chemical indicators to ensure the reliability and generality of the results.

There exist some limitations to this study. First, this is a single-center, small scale RCT. Second, the follow-up duration is relatively short. Third, this trial will be performed in Beijing, China, there may be regional and ethnic deviations. Thus, if we finally get a promising result from this current, we consider conducting a multicenter, randomized, large scale, and long follow-up trial in order to provide more significant information to guide clinical treatment.

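### Stratifying 60 patients on four factors gives at least 16 sparse strata: balance still improves at that minimum, but most of the gain goes if levels are finer, and no named test is tied to the factors

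*Protocol article*

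**What the plan says.** Study design fixes the sample: "A total of 60 patients diagnosed with UA are eligible for enrolment". On allocation, the same section adds that "they will be randomly allocated to the treatment group or the control group in a 1:1 ratio". The Discussion confirms that "this is a single-center, small scale RCT", so no centre factor is added. Under Randomization and masking, an investigator "will use an interactive Web response system to randomly allocate participants to receive either LFN-G or placebo after enrollment in a 1:1 ratio". The stratification is set out next: "Randomization will be stratified by age, sex, morbid status, and comorbidities". Levels, cut-points and block size are not given, and minimisation is not mentioned. The eligible age range is "18 to 80 years old".

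Under Statistical analysis, "the measurement data is expressed as mean ± standard deviation and tested by" a t test or q test. For binary outcomes, "Chi-square test is used for counting data", and ordered data go to a rank sum test. Logistic regression is named for situations with several factors, next to Spearman correlation for single ones. It has no covariate list and no stated link to the comparison of arms or to the four stratification factors.

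**The concern.** Stratified allocation balances the arms only as far as blocks are completed within strata. When the average stratum is smaller than one block, many strata end part-way through a block. These leftovers add up across strata, both in the arm totals and within each factor level. With about 30 patients per arm, a chance imbalance in a prognostic factor can produce or hide a difference.

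The analysis side is separate. Balancing on prognostic factors makes the estimated difference less variable, but an unadjusted test still uses the full outcome variance. The precision gained by design is then not used.

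**Working it through.** **Inputs from the article.** N = 60, 1:1, one centre, four factors. The article states no number of strata, so there is no plan figure to reproduce.

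**Assumed inputs.** Levels per factor (two each as the minimum, then finer splits), permuted blocks of 4 within strata, and equally likely levels. Blocks of 2 and skewed prevalence serve as sensitivity checks.

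**Step 1: strata.** The count is the product of the levels.
- 2 x 2 x 2 x 2 = 16; 60/16 = 3.75 patients per stratum.
- 3 x 2 x 2 x 2 = 24; 60/24 = 2.5.
- 3 x 2 x 3 x 2 = 36; 60/36 = 1.67.
- 3 x 2 x 3 x 4 = 72; 60/72 = 0.83.

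Only the 16 follows from the text.

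**Step 2: how full the strata are.** With 16 equally likely strata, a stratum's size is binomial(60, 1/16). P(0) = (15/16)^60 = 0.021, and P(1) + P(2) + P(3) = 0.083 + 0.164 + 0.211 = 0.458. The share of occupied strata smaller than one block of 4 is 0.458/(1 - 0.021) = 0.47 (46% to 47% in simulation). This is not the share ending in an incomplete block, meaning a size that is not a multiple of 4, which is about 77%.

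**Step 3: balance.** Simulation, 1,500 to 3,000 trials per setting; ranges show the spread between runs.

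| Strata | Smaller than one block | End incomplete | Arms differ by 6 or more | Some factor level off by 6 or more |
|---|---|---|---|---|
| 16 | 46-47% | 77% | 16-17% | 17-18% |
| 36 | 89% | 92% | 34-36% | 56-58% |
| 72 | 98% | 99% | 44-45% | 73-77% |

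At 24 strata, the arms differ by 6 or more in 29% and a factor level in 39%.

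Comparators:
- Simple randomisation: arms differ by 6 or more in 52% (exact binomial, 2 x P(X ≤ 27) with n = 60). A factor level is off by 6 or more in 83% to 84% with the levels of the 16-stratum case and 87% with those of the 72-stratum case.
- Unstratified blocks of 4: arm totals equal; a factor level off by 6 or more in 49% to 50% with the 16-stratum levels.
- Minimisation with a 0.8 biased coin: arms differ by 6 or more in under 1%, a factor level in about 5% to 12%. One set of runs gave 2% to 3%, so the larger range is the cautious one.

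Mean difference between arms within a factor level:

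| Strata | Stratified blocks of 4 | Unstratified blocks of 4 | Simple | Gain over simple |
|---|---|---|---|---|
| 16 | 2.1 | 3.1 | 4.4 | 2.3 |
| 36 | 2.8 | 3.0 | 3.9 | 1.1 |
| 72 | 3.1 | 2.9 | 3.7 | 0.6 |

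The gain over unstratified blocks goes from 1.0 to 0.2 to -0.2. The mean difference in arm totals is 2.8, 4.5 and 5.2 at 16, 36 and 72 strata, against 0 for unstratified blocks and about 6.3 for simple randomisation.

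**Step 4: unadjusted test.** Type I error of a t test at nominal 5% after stratified blocks of 4 (8,000 trials per setting), when the factors explain 0%, 20% and 40% of outcome variance:
- 16 strata: 5.3%, 3.6%, 2.1%.
- 72 strata: 5.2%, 4.8%, 3.8%.

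The Monte Carlo standard error is sqrt(0.05 x 0.95/8000) = 0.24 percentage points, so 5.3% is compatible with 5%. Only the t test was simulated; the same direction is expected for the other unadjusted tests.

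**The case against.** A reader might infer that stratification cannot deliver balance here. At 16 strata, the only count that the article supports, this is wrong. A factor level is badly off in about 17% of trials, against 84% under simple randomisation and about half under unstratified blocks. With blocks of 2 it is 3%, with arms differing by 6 or more in 7%. That part of the objection stands.

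A reader might also infer more strata than patients. That needs levels such as 3 x 2 x 3 x 4, which the article does not state; morbid status and comorbidities could each be yes or no. Even at 72 strata, blocks of 2 give arms differing by 8 or more in 19% of trials, against 37% for simple randomisation, though a factor level is still off by 6 or more in 53%. With skewed prevalence at 72 strata, the mean factor-level difference is 2.8 against 5.2 for simple randomisation, but unstratified blocks also give 2.8. So the bad case is conditional.

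An article may leave level definitions, block size and the algorithm to the full protocol, and their absence is not the criticism. The choice of four factors for 60 patients is stated. If the Web system already minimises, the sparse-strata problem disappears and the sentence under Randomization and masking needs correcting.

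Finally, it goes too far to say that the analysis must ignore the factors. Logistic regression is named, and an analysis plan that is not shown may set the adjustment. What stands is that nothing in the article ties any comparison of arms to them.

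**Conclusion.** The point holds as a matter of efficiency and reliability, not of validity. Four factors for 60 patients force at least 16 strata averaging 3.75 patients. At that minimum, stratification still works on the factors but leaves an avoidable risk, about 16%, that the arms differ in size by 6 or more. At 36 to 72 strata the risk is about 35% to 45%, and the gain in factor balance over unstratified blocks is nearly or wholly gone. These figures rest on blocks of 4 and equal prevalence; smaller blocks or skewed prevalence soften them.

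Tests that do not use the factors become conservative when the factors are prognostic, down to 2.1% in the most marked case examined, so power is lost. A reader might fear false positives from ignoring the factors; the calculation shows no inflation beyond simulation error.

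**What to change.** Under Randomization and masking, take one of two routes:
- state that the Web system uses minimisation with a random element (for example, probability 0.8 for the favoured arm) over the four factors, with their levels defined; or
- keep only one or two binary stratification factors.

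Under Statistical analysis, adjust the comparisons of continuous outcomes for the factors used in allocation. For the binary primary composite, adjust only for one or two of these factors, named in advance, for example with a stratified Mantel-Haenszel analysis. The article gives no event rate, and with few events in 60 patients a logistic model with four or more covariates could be unstable.

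The cost is reconfiguring the Web system before the first patient is randomised, two changed sentences, and slightly more analysis work.

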### Test drugs

2.8

Drugs for clinical trials are LFN-G and placebo (LFN-G mimics), provided by the Guangdong E-Fong Pharmaceutical Technology Development Co, Ltd (Guangdong, China). Formula ingredients of LFN-G includes: Lumbricus (Di long) 10 g, Radix Clematidis (Wei lingxian) 15 g, Radix Cynanchi Paniculati (Xu changqing) 12 g, Panax notoginseng (San qi) 3 g, Astragalus (Huang qi) 10 g, and Borneol (Bing pian) 0.1 g. All ingredients are herbal granules. These granules are mixed and packaged into 2 single-dose sachets, each weighing 25.05 g. The placebo consists of medical starch dextrin without active ingredients. Through adding a variety of food colorings and flavouring agents, the placebo will present a similar weight, appearance and taste as close as possible to the real LFN-G.

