### Treatment plan

3.1

All participants will receive a standard western medicine treatment in accordance with guidelines^[2,5,6]^ judged by a senior cardiology physician, including but not limited to anti-myocardial ischemia therapy, antiplatelet or anticoagulation therapy, statin therapy. Meanwhile, all participants will accept lifestyle adjustments.

Experimental group: Participants will receive LFN-Gs (divided into 2 equally- weight in separate packages, each 25.05 g), dissolving each package in 100 mL warm boiled water after breakfast and supper for 4 weeks.

Control group: Patients will be given placebo granules (divided into 2 equally- weight in separate packages, each 25.05 g). The administration is in accordance with the experimental group.

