### Outcome measures

3.3

Primary outcome is the incidence of major cardiac adverse events, defined as a composite of recurrent angina, acute myocardial infarction, severe arrhythmia, heart failure, and cardiac death. This outcome will be compared with the baseline and the 4th week.

Secondary outcomes including:

(1)Seattle angina scale score: This score includes 4 aspects (physical activity limitation, angina frequency, treatment satisfaction, and disease cognition) and it can provide information of participants’ subjective assessment of therapy. This outcome will be compared the baseline with the 1st, 2nd, 3rd, and 4th week.(2)Chinese medicine syndromes: This outcome will be compared the baseline with the 1st, 2nd, 3rd, and 4th week.(3)ECG: The change of St-segment and T wave of baseline and the 1st, 2nd, 3rd, and 4th week.(4)Myocardial nuclides perfusion: It will be used to evaluate myocardial perfusion under endocardium and epicardium of the baseline and the 4th week.(5)Echocardiography: Measurement of wall motion score index and left ventricular ejection fraction of the baseline and the 4th week.(6)Vitro measurement: Measurement of serum inflammation factors such as C-reactive protein, high sensitive-C-reactive protein, interleukin-6, matrix metalloproteinase-9, and so on.

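### A look-alike placebo is made but the trial runs open-label without a stated reason, leaving recurrent angina and the other symptom-based or read outcomes open to expectation and reporting bias

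*Protocol article*

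**What the plan says.** Section 2.2 labels the design: "This present study is a prospective, open-label, randomized, placebo-controlled clinical trial". The abstract, the Introduction and the Discussion use the same label, so it is the intended design and not a slip in one place. Section 2.4 (Randomization and masking) states: "Due to this trial is an open-label trial, so neither participants nor investigators is not masked to the treatment option". The double negative literally says the reverse of open-label, but the first half of the sentence leaves no doubt about the meaning.

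Section 2.8 (Test drugs) describes the comparator: "The placebo consists of medical starch dextrin without active ingredients", with colouring and flavouring added so that "the placebo will present a similar weight, appearance and taste as close as possible to the real LFN-G". Section 3.1 gives both arms two packages of 25.05 g each and says of the control arm: "The administration is in accordance with the experimental group". On allocation, section 2.4 says: "A designated investigator of our team will use an interactive Web response system to randomly allocate participants to receive either LFN-G or placebo".

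Section 3.3 gives the primary endpoint as major cardiac adverse events, "defined as a composite of recurrent angina, acute myocardial infarction, severe arrhythmia, heart failure, and cardiac death". The secondary outcomes include the Seattle angina scale, Chinese medicine syndromes, ST-segment and T-wave changes, perfusion imaging, echocardiography and serum inflammation markers.

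The article gives no reason for not masking and mentions no masked reader or event adjudication. The limitations in section 4 are single centre and small size, short follow-up, and region and ethnicity.

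**The concern.** The main purpose of a placebo that looks and tastes like the active product is to hide the arm. Here the look-alike is made, packed and given identically, and then the arm is disclosed. Control patients know they are taking starch dextrin, and the staff who record angina, score syndromes and read ECGs know the arm too.

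This reaches the primary endpoint. Recurrent angina is a symptom-based event. In 60 patients with unstable angina followed for 4 weeks, with NYHA class IV heart failure and several severe arrhythmias excluded at entry (section 2.6), it is plausibly the most frequent of the five components. A difference in what patients mention, or in what unmasked clinicians count, would then look like a treatment effect. The Seattle score, which section 3.3 itself describes as a subjective assessment by the participant, is exposed in the same way.

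The Introduction justifies the trial by the lack of a rigorous randomised trial of LFN-G. Masking is the feature that would most help to meet that aim, and no later analysis can restore it.

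**Working it through.** **Reading the sections together**

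| Needed for masking | In the protocol article |
|---|---|
| Indistinguishable comparator | Yes, as far as matching succeeds (2.8) |
| Same sachets and schedule | Yes (3.1) |
| Central allocation system | Yes, run by a team investigator (2.4) |
| One supplier for both products | Yes (2.8) |
| Coded labels, held code, code-break | Not described |
| Reason for not masking | None beyond the circular sentence (2.4) |

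Most of what masking needs is already in place.

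**Size: a sensitivity calculation**

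The article gives no event rate, effect size or power for its sample of 60, so there is no stated figure to reproduce.

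Inputs from the article: 60 patients at 1:1, so 30 per arm (2.2); chi-square test for counts, two-sided, 0.05 (3.7). Assumed inputs: no true effect of LFN-G, and recorded risks pC (control) and pT (LFN-G) that differ only because the arm is known.

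With y control events, x LFN-G events and s = x + y, the uncorrected statistic is

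X² = 60(y − x)² / [s(60 − s)],

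and with continuity correction |y − x| is replaced by |y − x| − 1. The rejection probability is the sum of Bin(y; 30, pC) × Bin(x; 30, pT) over all pairs with X² > 3.84.

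| Recorded risk, control vs LFN-G | Uncorrected | Corrected |
|---|---|---|
| 40% vs 40% (no shift) | 4.9% | 2.6% |
| 40% vs 30% (10 points) | 12.3% | 7.8% |
| 45% vs 25% (20 points) | 36.3% | 27.2% |

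Normal-approximation check of the uncorrected column, with pooled risk 0.35 in both shifted rows and √(2 × 0.35 × 0.65/30) = 0.1232:
- 10 points: z = (0.10 − 1.96 × 0.1232)/√[(0.24 + 0.21)/30] = −0.1414/0.1225 = −1.15, giving about 12.4%.
- 20 points: z = (0.20 − 0.2414)/√[(0.2475 + 0.1875)/30] = −0.0414/0.1204 = −0.34, giving about 36.6%.

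The same enumeration (uncorrected) with a fraction u of events unrecorded in the LFN-G arm only, so pT = pC(1 − u):

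| pC | u = 20% | u = 30% | u = 40% |
|---|---|---|---|
| 0.2 | 6.8% | 9.4% | 13.5% |
| 0.3 | 8.0% | 12.3% | 18.9% |
| 0.4 | 9.5% | 15.9% | 25.8% |
| 0.5 | 12.3% | 21.7% | 35.1% |

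With u = 0 the rate is 4.9% to 5.2%. On this scale the 10-point case is u = 10/40 = 25% and the 20-point case is u = 20/45 = 44%, which is beyond the largest u in the table. Nearly all the excess favours LFN-G, because the assumed shift runs that way.

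For a continuous score analysed by t test (58 degrees of freedom), an expectation shift of d standard deviations gives noncentrality d√(30/2): 1.16 for d = 0.3 and 1.94 for d = 0.5. The rejection rates are 20.8% and 47.8%.

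**The case against.** A reader might infer that an open placebo controls nothing, that no positive result could be credited to LFN-G, and that masking would remove the bias. The documents support none of these.

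- Identical sachets and schedule still equalise sachet burden and attention. What is lost is control of expectation and reporting.
- Outcomes are not equally exposed. Cardiac death, infarction and the serum assays are less open to expectation than recurrent angina. Perfusion, ejection fraction and wall motion could be protected by masked readers alone.
- Section 2.8 promises similarity only as far as achievable. Taste or smell may still reveal the arm to some patients.

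The other side has further points. Section 3.3 gives no component rates and no method of ascertaining recurrent angina, and a condensed article may leave event definitions to the full protocol. That recurrent angina dominates is therefore inference. The shifts have no source in the documents, the 20-point case is large, and section 3.7 does not say whether the chi-square test is corrected. Background therapy is tied to guidelines (3.1), so unmasked discretion over it is bounded. No costs are stated, and kit coding, code custody and code-break would be new procedures.

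All of this stands, and it limits the size and reach of the point. It does not explain why a matched placebo is made and then not used for masking.

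**Conclusion.** The point holds in limited form. The protocol provides a look-alike placebo, identical administration and Web allocation, but runs open-label without a reason and does not list this among its limitations. The exposure lies in recurrent angina within the primary composite, the Seattle score, the Chinese medicine syndrome outcome and ST-T reading.

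The size is a sensitivity range, not an estimate. With no true effect and 30 per arm, the error rate rises from about 5% to about 12% for a 10-point shift and about 36% for a 20-point shift (uncorrected), or from about 3% to about 8% and 27% (corrected). Selective under-recording of 20% to 30% gives about 7% to 22%. These figures assume that the shift favours LFN-G, and the dominance of recurrent angina is plausible but undocumented. That the bias is possible, and that masking would limit it, does not depend on the exact percentages.

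The double negative in section 2.4 is an editorial matter and adds nothing to the weight of the point.

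**What to change.** Before enrolment, change the design to double-blind in the abstract, the Introduction, sections 2.2 and 2.4, the Discussion and the registry entry. In section 2.4 specify that:

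- the manufacturer, which already supplies both products, labels sachets with kit numbers only;
- the Web system returns a kit number instead of an arm name, holds the code and provides emergency code-break;
- participants, treating clinicians, and those who assess outcomes or read ECG, echocardiography and perfusion stay masked until database lock.

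Rewrite the double-negative sentence under whichever design is kept.

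The cost is labelling, code custody, a code-break procedure, and an ethics and registry amendment, for which section 2.1 already gives the route. No extra patients or visits are needed.

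Section 2.3 plans recruitment from June 2020, and the change is simple only before the first patient is allocated. If masking is truly not possible, state the reason, use masked readers for ECG and imaging, and add the lack of masking to the limitations. That would protect the read outcomes but would not correct what patients report.
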